## Methods

The present pilot study aims to investigate the situation of patients who are in opposition and to understand why they are opposing. The design is therefore prospective and monocentric. The protocol presented is based on the SPIRITS guidelines [30]. It was adapted in order to take into account the mixed methodology of the study and guidelines of pilot and feasibility studies [31, 32]. The objective is to explore participants’ positioning following diagnostic or therapeutic procedures that they declined. More specifically, characteristic components of these medical situations and arguments of the various protagonists were identified to understand the representations and symbolic functions linked to the opposition to medical acts. The study is divided into 2 parts:
An epidemiological survey aiming to identify situations with opposition to diagnostic or therapeutic medical procedures in an acute geriatric wardA comprehensive study with a qualitative methodology based on semi-structured interviews that were conducted with carers or relatives involved in the aforementioned situations, to gain a more specific understanding of the factors involved in opposition to diagnostic or therapeutic procedures

### Definition of opposition

To date, there is no scientific consensual definition of opposition to treatment or diagnostic procedures. In the OPTAH study, we will define opposition to treatment or diagnostic procedures as follows:
The repeated (at least twice in a row, with at least two separate interlocutors) and explicit (verbal or physical) expression of an opposition. Oppositions expressed during the usual meetings between doctors and patients are not included in the analysis if they are part of a free and informed choice, even if they may concern a decision (acceptance or refusal) of a therapeutic proposal. Opposition behaviors concern either of the following:
Medication intakeInvasive diagnostic or therapeutic procedures (biological check-up, imaging, endoscopy, biopsy, etc.)Removal by the patient of a venous, nasogastric, or urinary catheterIn the absence of consent or acceptance by the patient of similar treatments during the reporting period

It should be noted that we will not include in this definition non-medical care (meals, shower, massage, physiotherapy) if it does not have medical consequences, to avoid confounding factors and information gathering issues. Opposition to non-medical care deserves separate research studies. Thus, patients who oppose treatments or diagnostic procedures will be included in the study even though they otherwise accept non-medical care. Symmetrically, patients who do not oppose treatments and diagnostic examinations but who refuse care (meals, shower, massage, etc.) will not be included in the study unless their refusal (e.g., to drink) may lead to the development of a medical pathology (e.g., functional kidney failure due to dehydration) or medical consequences, for which they refuse medical investigation or treatment.

### Study objectives

Epidemiological component: In the epidemiological survey, the objective will be to identify and establish the frequency of situations in which patients will express opposition to treatment or diagnostic procedures. The data will be obtained in the acute geriatric ward of a French university hospital, over 1 year.Comprehensive component: During the semi-structured interviews with carers and relatives involved in the epidemiological component, the objective will be to identify, describe, and understand the meaning of the opposition to treatment or diagnostic procedures expressed by patients included in the study (see below).

### Population and duration of the study

Patients over 75 years of age who will oppose diagnostic or therapeutic procedures during hospitalization and who will be hospitalized in the acute geriatric ward of a French university hospital will be included in this study. The acute geriatric care department comprises 54 hospitalization beds spread over 2 sections, including 6 geriatric intensive care beds. Medical care is provided with a ratio of one doctor and one intern for every 12 patients in conventional beds and 1 for every 6 patients in the geriatric intensive care unit.

To obtain an exhaustive overview of this population, the epidemiological data collection will involve a standardized survey that includes questions on descriptive characteristics of patients, which will be reported at the time of admission and during a follow-up in geriatric hospital services (collection of medical history, treatments, medico-social data, standardized geriatric assessment). A 1-year recruitment period will be used in this study. Among the patients that will present opposition to treatment or diagnostic procedures, we will select patients that can be interviewed (i.e., without cognitive impairment or with mild to moderate neurocognitive disorders which are not predominantly phasic) for the comprehensive (qualitative) component of this study. It is anticipated that recruitment for interviews could be difficult in this population, and the inclusion period for the second component is 2.5 years. The epidemiological data of patients included in the second year of the comprehensive component will be added to the initial data to allow comparisons between the groups participating in the two components. We will thus verify that for the population included in the comprehensive component, the characteristics of the opposition are similar to those of the overall study population.

The total duration of the study will therefore be 30 months.

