### Data collection strategies

#### Recruitment

This study aims to investigate opposition situations. To make a rigorous analysis, it seems necessary to do an exhaustive census of opposition situations. In that way, we will quantify the number of situations in which there is opposition to diagnostic or therapeutic procedures handled in the department for 1 year.

Given the population and the subject of this study, it is foreseeable that opposition to participation will occur, even though our focus on the refusal and thus the interest and respect for the person’s will can facilitate exchanges. This concern justifies the extension of the comprehensive study for an additional year and a half.

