## Study status

The recruitment period began on 1 January 2018 and therefore extends, for the comprehensive part, until 30 June 2020. After 20 months of data collection, the quantitative collection comprised 33 situations in the epidemiological component, of which 5 situations were included in the qualitative component (interviews).

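### Interview patients recruited after the one-year census are added to the census data and then compared with a population that contains them

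*Protocol article*

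**What the plan says.** The protocol article sets one window for the epidemiological part. Under Study objectives, on frequency: "The data will be obtained in the acute geriatric ward of a French university hospital, over 1 year". Under Recruitment, which calls for an exhaustive count: "we will quantify the number of situations in which there is opposition to diagnostic or therapeutic procedures handled in the department for 1 year". Under Population and duration of the study: "A 1-year recruitment period will be used in this study".

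The interview (comprehensive) part has a longer window. The same section on population and duration says "the inclusion period for the second component is 2.5 years", because recruitment for interviews is expected to be hard. It then states: "The epidemiological data of patients included in the second year of the comprehensive component will be added to the initial data". The reason given is "to allow comparisons between the groups participating in the two components", and the intended check is that, for interviewed patients, "the characteristics of the opposition are similar to those of the overall study population".

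The two parts have different entry conditions. The epidemiological part needs only a qualifying opposition in the department and no objection to use of the data. The interview part also needs signed consent, a Mini-Mental score above 10 and no phasic disorder (Inclusion criteria, Exclusion criteria).

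Statistical analysis of epidemiological data plans one descriptive analysis, with chi-square and Student's tests, and a comparison with 60 reference patients from the same service. It does not separate later entrants. Study status reports: "After 20 months of data collection, the quantitative collection comprised 33 situations in the epidemiological component". Five of these were in the interview part, and no 12-month count is given.

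**The concern.** On the stated periods, months 1 to 12 give an unselected series and later months give only patients who could be, and agreed to be, interviewed. Adding the second group to the first produces a data set that is neither a one-year census nor a consecutive series. Cognitive status is among the characteristics to be described and is central to the study's hypotheses, and it is also one of the characteristics on which late entrants are selected.

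Two results are exposed. The first is the description of patients who oppose care, and with it any comparison with the 60 reference patients. The second is the check that interviewed patients are typical. Its comparator contains the interviewed patients, so the two sides are pulled together and the check leans towards the answer it is meant to test.

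A related loose end is that the only count reported covers 20 months, so a reader cannot recover the one-year numerator.

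**Working it through.** The article gives no sample size, power or expected frequency, so there is no planned figure to reproduce. The inputs are:

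- 33 situations at 20 months, 5 of them interviewed (Study status)
- a 12-month census (Study objectives, Recruitment)
- about 10 planned interviews (Comprehensive part)
- the prevalence of a trait that bars interview, such as a Mini-Mental score below 10. The article does not give it, so 20%, 30% and 50% are assumed.

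**1. Census count if only interview patients entered after month 12.** Late entries are then a subset of the 5 interviewed, so they number 0 to 5.
- Census count: 33 − 5 = 28 up to 33 − 0 = 33
- Late share: at most 5/33 = 15.2%
- Overstatement if 33 were read as the annual count: 33/33 − 1 = 0% to 33/28 − 1 = 18%

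**2. Census count if all cases were collected for 20 months.**
- Annualised count: 33 × 12/20 = 19.8, with an exact Poisson 95% interval of 13.6 to 27.8
- Overstatement if 33 were read as the annual count: 33/19.8 − 1 = 67%

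This reading contradicts the one-year window in the three sections quoted above. It also removes the selection problem, because late cases would then be unselected. Steps 1 and 2 are alternatives and cannot both apply.

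**3. Shift in the case profile under step 1.** With c census cases, a late entries without the trait, and census prevalence p, the pooled share is p × c/(c + a). For c = 28 and a = 5, the maximum at 20 months:

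| Assumed p | Pooled share | Shift (points) |
|---|---|---|
| 20% | 0.20 × 28/33 = 17.0% | 3.0 |
| 30% | 0.30 × 28/33 = 25.5% | 4.5 |
| 50% | 0.50 × 28/33 = 42.4% | 7.6 |

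If all 10 planned interviews fell after the census (an assumed upper case), late entries would be 10/38 = 26%. A 30% trait would then fall to 0.30 × 28/38 = 22.1%, a shift of 7.9 points. If all five interviewed patients entered in year 1, the shift at 20 months is zero.

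**4. Overlap in the similarity check.** For n interviewed among N in total, the difference between interviewed and overall equals (1 − n/N) times the difference between interviewed and non-interviewed.
- 5 of 33: factor 28/33 = 0.85, so the true contrast is shrunk by 15%
- 10 of 38: factor 28/38 = 0.74, so it is shrunk by 26%

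The first figure holds whenever the five were recruited. Adding late interview patients increases the overlap. In their usual two-sample form, the chi-square and Student's tests also assume groups that do not overlap; the article does not say which test this check uses.

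**The case against.** The strongest reply is that the addition has a stated and limited purpose, comparison between components, and that the frequency is tied to one year in two other places. This stands. A reader might infer that the plan puts late interview patients into the one-year frequency, or that the frequency is inflated 1.67-fold. The documents do not support either reading. No sentence places late entrants in the frequency. The 33 is a progress count, labelled as covering 20 months and not divided by any denominator. The 1.67 ratio needs full collection for 20 months, which is incompatible with late entry through interviews only.

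It can also be said that the profile shift is small beside sampling error. At 50% among 28 cases the 95% margin is about 1.96 × √(0.25/28) = 18.5 points, against a shift of at most 7.6. This is fair, and it argues against a high rating. But the shift has a known direction and is avoidable.

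Comparing a subgroup with the whole is a common description of representativeness, and with about 10 interviews the check can only be descriptive. That limits the harm without removing the bias towards similarity.

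Finally, this is a condensed article on a single-centre pilot. Its flow and planning figures are not shown, and a fuller plan may say which records feed which table. Silence on that would be no finding. The rule to add the data and the choice of comparator are, however, stated in the text.

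**Conclusion.** The concern holds for the case profile and for the similarity check. As written, the plan adds patients selected on consent, cognition and language to an unselected census, then compares them with a population that includes them. At the 20-month figures, up to 5 of 33 cases (15.2%) can be late, selected entries. A trait that bars interview would be understated by up to 3.0 to 7.6 points over assumed prevalences of 20% to 50%, and the similarity contrast is shrunk by about 15%. These sizes assume that only interview patients entered after month 12, and the profile shifts also assume that all five interviewed patients did so.

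For the frequency, the documents leave a reporting gap and do not state a faulty analysis. The census count is 28 to 33 if the stated rule was followed. If collection of all cases ran on, the annualised count is about 19.8 and the status section conflicts with the one-year window. The article does not let a reader decide between them.

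Severity is moderate: the study is a descriptive pilot, and the effect is limited in size but systematic and easily avoided.

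**What to change.** - Define the epidemiological cohort as first qualifying oppositions dated 1 January to 31 December 2018. This takes the census year to start with recruitment on the date given in Study status. Use only this cohort for frequency, case description and comparison with the 60 reference patients.
- Flag patients who enter later through the interview component and report them in a separate column. Apply this to month 30: the present rule names only the second year, although the extension lasts an additional year and a half.
- Replace the comparison with the overall study population by interviewed patients against non-interviewed census patients.
- Split the 33 situations into the first 12 months and the following 8, and say whether anyone other than interview patients was entered after month 12.

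The cost is a date filter, a flag and a few sentences. The descriptive sample becomes slightly smaller, by at most 5 of the 33 at 20 months if the stated rule was followed.

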**Fig. 1 Fig1:**
[figure not shown]
Inclusion flow diagram

For the comprehensive (qualitative) part, the inclusion criteria include patients, carers, and relatives who:
Signed an informed consent formCan participate in a semi-directive interview with the researcher (the Mini-Mental States > 10, no phasic disorders)

Patients under legal protection are considered vulnerable. Their dependency is higher, and fundamental decisions concerning their care are most often taken by substitutes. However, these patients can still express opposition to care in various ways. Since they are under legal protection, listening to the expression of their will allows a better understanding of their precarious condition. As such, their integration into the research protocol is necessary. A specific information and consent form will be presented to the patient and guardian, and both consents will be obtained.

As this study will be a pilot study, we will include patients with all forms of cognitive status. More specific studies should be developed in the future.

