#### Comprehensive part

Among patients presenting an opposition, we will select about ten situations that will be included in the comprehensive part of the study, to explore these situations through qualitative methodological tools (interviews, surveys, and observations). All epidemiological data will also be collected for these patients.

Thus, a comprehensive data collection will be conducted as follows:
A semi-directed interview will be carried out with the patient, a relative designated by the patient, and the usual carer at home or the healthcare institution. These interviews (3 per situation) will be conducted by a researcher, a psychologist, or a sociologist (the complementarity of the two scientific disciplines allows triangulation of data collected in the various interviews), according to a pre-established interview framework (see Table 1).Medical questionnaire for the general practitioner (1 per situation). The qualitative medical form will be completed by the investigating physician during a telephone call with the family physician.As soon as the opposite situation leads to difficulties in medical care, and as soon as the setting up of collegial meetings will be organized, these meetings (at least 1 per situation) will also be attended by a psychologist and a sociologist of the research team. They will use an observation matrix to describe the content of collegial meetings, as observers (non-participants) in the discussion*.*

**Table 1 Tab1:** Themes to be used during semi-structured interviews

Themes to be used during semi-structured interviews	
**History of care**	History of hospitalization
	Medical decisions
**Relationship with the caregiver**	Precedence of medical decisions
	Relationship with health professionals
**Home living/medicalization**	Relatives
	Home carer
	General practitioner
	Dependency
**Representation**	Previous experience with the illness, hospitalizations, treatments, operations

About 10 patients will be included in the comprehensive study. The sample could be re-evaluated if there is no data saturation, or if there are some difficulties to collect data because of patients’ cognitive status.

The verbatims will be analyzed according to the principles of the grounded theory (see below).

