### Data analysis

#### Statistical analysis of epidemiological data

Analyses for the quantitative component are based on the data that will be extracted from medical records and descriptive statistics calculated based on this data.

The data of the reference population for statistics on prevalence and comparisons with the general population will be determined according to results obtained in a survey of professional practices conducted within the same geriatrics service. An anonymized database was therefore created to compile the medical and socio-demographic data of 60 patients that were seen in this ward for 1 month. These patients are representative of the population that receives health services in this hospital, which allows comparisons with the study group.

A descriptive analysis of the data will be conducted. Patient characteristics will be described using mean and standard deviation (SD) or median and interquartile range (IQ) for quantitative variables and using counts and percentages for qualitative variables. Variables will be compared using either the chi-square test or Student’s test. A difference with a *p* less than 0.05 will be considered significant. The R software will be used for these analyses.

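### With about 10 interviewed patients, a non-significant difference test cannot verify that their opposition resembles that of the overall study population

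*Protocol article*

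**What the plan says.** The Protocol article, under Population and duration of the study, explains that epidemiological data from the later inclusion period are added to the first-year data "to allow comparisons between the groups participating in the two components". It then states the purpose: "We will thus verify that for the population included in the comprehensive component, the characteristics of the opposition are similar". The comparator named there is the overall study population.

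Four other places bear on this check.

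- **Size.** Comprehensive part: "About 10 patients will be included in the comprehensive study". The article allows this number to be revisited if saturation is not reached. Study status reports 33 situations after 20 months, 5 of them interviewed.
- **Nesting.** Interviewed patients are chosen from those who show opposition, and Comprehensive part adds: "All epidemiological data will also be collected for these patients". Study status also counts the 5 among the 33.
- **Rule.** Statistical analysis of epidemiological data: "Variables will be compared using either the chi-square test" or Student's test, where a difference with a p-value "less than 0.05 will be considered significant". The same section announces a descriptive analysis. It gives no margin, effect measure or interval for judging similarity.
- **Selection.** Under Inclusion criteria, interviewees must sign consent and be able to take part in an interview ("the Mini-Mental States > 10, no phasic disorders"). The pilot as a whole admits patients of any cognitive status.

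**The concern.** A difference test can give evidence against similarity. A non-significant result is evidence for similarity only if the test would probably have found a difference worth caring about. With 5 to 10 patients in one arm, it would not.

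Two features add to this. If the subset is compared with the whole that contains it, the groups share patients. Chi-square and Student's tests assume independent groups, and the overlap pulls the two summaries together. Also, interviewees are selected on cognition, language and consent, so their form of opposition (argued verbally, as against physical resistance or catheter removal) may well differ from that of the others. The documents do not show that it does, but this is the kind of difference the check should be able to reveal.

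At stake is a statement in the results that the interviewed patients' opposition is similar to that of the overall study population, made on data that could not have shown otherwise.

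**Working it through.** The article gives no power or sample size for this comparison, so there is no stated figure to reproduce.

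**Inputs from the article.** About 10 interviewed patients planned; 5 of 33 at 20 months; chi-square or Student's test; threshold 0.05.

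**Assumptions.** Tests are two-sided. The total at 30 months is about 50, from 33 / 20 × 30 = 49.5 at a constant rate. The illustrative true frequencies of an opposition characteristic are 20% in interviewed and 50% in the other patients.

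**Step 1: effect of the overlap.** With n₁ interviewed among N, the whole has expected frequency (n₁p₁ + (N − n₁)p₂)/N. The expected difference between subset and whole is therefore (p₁ − p₂)(1 − n₁/N).

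- 5 of 33: shrinkage 5/33 = 15%, so 30 points become 25.5.
- 10 of 50: shrinkage 10/50 = 20%, so 30 points become 24.

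**Step 2: probability of p < 0.05.** All outcomes (a of n₁, b of N − n₁) are enumerated with binomial probabilities, and the probabilities of outcomes where the chi-square test rejects are summed. The nested version tests a/n₁ against (a + b)/N as if independent. The disjoint version tests a/n₁ against b/(N − n₁). Each cell gives the result with / without continuity correction.

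| True frequencies (interviewed, others) | Groups | 5 of 33 | 10 of 33 | 10 of 50 |
|---|---|---|---|---|
| 50%, 50% (type I error) | nested | 0.1% / 2.0% | 0.2% / 0.7% | 0.5% / 1.8% |
| 50%, 50% (type I error) | disjoint | 1.1% / 5.0% | 2.2% / 4.6% | 1.9% / 5.5% |
| 20%, 50% | nested | 0.6% / 9.6% | 4.9% / 14.5% | 11.2% / 24.4% |
| 20%, 50% | disjoint | 5.7% / 20.7% | 21.2% / 35.4% | 24.1% / 42.2% |
| 20%, 70% | nested | 19% / 46% | 31% / 51% | 56% / 74% |

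In the nested analysis a true 30-point difference is missed in about 76–99% of studies (100 − 24.4 to 100 − 0.6). In the disjoint analysis it is missed in about 58–94% (100 − 42.2 to 100 − 5.7).

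**Step 3: continuous characteristics.** Student's t-test with 10 of 50 and a standardised difference of 0.5 has power of about 14% nested and 28% disjoint. At 0.8 the figures are 39% and 60%.

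**Step 4: precision of the disjoint difference.** The 95% half-width at 50% is 1.96 × √(0.25/n₁ + 0.25/n₂).

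- 10 versus 40: 1.96 × √(0.025 + 0.00625) = 0.346, about ±35 points.
- 5 versus 28: 1.96 × √(0.05 + 0.00893) = 0.476, about ±48 points.

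**Step 5: what verification would take.** Assume an equivalence margin of 20 points, true frequencies of 50% in both groups, one-sided 0.05, 80% power and a 1:4 ratio. Then n₁ = (0.25 + 0.25/4) × (1.645 + 1.282)² / 0.20² ≈ 67 interviewed, with about 268 not interviewed. That is far beyond a study planning about 10 interviews.

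**The case against.** The strongest reply has four parts.

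**The test is inferred.** The sentence promising verification names no test, and the p < 0.05 rule is stated generically, just after a different comparison with a 60-patient reference database. This stands as a limit on certainty. But it is the only comparison rule in the article, and a purely descriptive comparison of about 10 patients could not verify similarity either. The comparator and the promise are fixed in the article, so a separate analysis plan could not rescue them at this size.

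**The groups may be disjoint.** The article speaks of groups participating in the two components, which could mean interviewed against not interviewed. This is a fair reading, although the next sentence names the overall study population. If it is right, the shrinkage and the reduced type I error disappear, but power for 20% versus 50% is still only about 6–42%.

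**Large differences would be seen.** A reader might infer that similarity will be concluded almost whatever the truth. The calculations do not support that. A 20% versus 70% difference is found in 56–74% of studies with 10 of 50, even nested.

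**The check is secondary.** It serves none of the three pilot objectives directly, and the qualitative part rests on saturation, not statistical representativeness. This stands and lowers the severity. A reader might also infer that selecting on cognition by itself contradicts the check. It does not, because the check concerns characteristics of the opposition, not cognition. A different form of opposition is plausible but not shown.

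**Conclusion.** The point holds in a limited form and should be fixed; it does not threaten the study. The promise to verify similarity cannot be kept with about 10 interviewed patients. Under the only comparison rule given, true differences of up to about 30 points would usually pass as similarity, whether the groups are nested or disjoint. Testing subset against whole as independent groups would make this worse, with a type I error of about 0.1–2% instead of 5%.

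This rests on three things the documents leave open: that the p < 0.05 rule applies to this check, the final counts (bracketed here by 5 of 33 and a projected 10 of 50), and the illustrative frequencies. The documents do not establish that the nested test will be run, or that interviewed patients do differ in how they oppose.

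**What to change.** - Compare interviewed with not-interviewed patients, so that the groups do not overlap. If wanted, add a comparison with patients who were eligible for interview but not interviewed, which separates the effect of eligibility from that of consent and choice.
- For each opposition characteristic, report the difference with a 95% CI in place of a p-value verdict. The intervals will be wide, which is the honest message. The change does not make similarity verifiable.
- Reword the commitment from verifying similarity to describing how interviewed patients differ from the others.
- State that the qualitative conclusions apply to patients who can be interviewed.

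The cost is some wording and a few table columns, with no new data for the main comparison. The small downside is that representativeness of the interviewed group can no longer be claimed.
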